**Vision**	
13.	To determine retinal cell layer thickness in treatment-naïve PD subjects compared to age- and sex-matched control subjects.
14.	To determine retinal cell layer thickness in treatment-naïve PD subjects compared to age- and sex-matched glaucoma subjects.
15.	To determine clinical correlates of structural retinal changes and functional tests, including visual, motor, non-motor and neuropsychological scores.
16.	To determine the effect of dopaminergic medication on retinal layer thickness and visual function.

### Study population

#### In- and exclusion criteria

Inclusion criteria consist of PD diagnosis by a movement disorders specialist according to Movement Disorder Society Clinical Diagnostic Criteria for PD, with a confirmed dopaminergic deficit by means of an 3,4-dihydroxy-6-18F-fluoro-l-phenylalanine (^18^F-FDOPA) PET scan.

PD subjects who are unable to provide written informed consent, who are unable to comply with study procedures, who have exclusion criteria for Magnetic Resonance Imaging (MRI), who have gastrointestinal exclusion criteria influencing gut microbiome composition, or whose PD diagnosis is rectified during follow-up, are excluded from the study cohort. A detailed overview of the applicable in- and exclusion criteria is provided in Supplementary Table 1.

#### Recruitment strategy

Participants are recruited via Parkinson Platform Northern Netherlands (PPNN), a collaborative network of PD treating neurologists in 13 medical centers in the northern part of the Netherlands. PPNN serves a total of approximately 5000 PD patients, with an incidence of 400 newly diagnosed PD patient within this network. Treatment-naïve de novo PD subjects who are willing to participate are referred to the University Medical Center Groningen (UMCG) to assess the in- and exclusion criteria. After inclusion and completion of the baseline assessments, patients return to their treating neurologist to continue care as usual, including the start with dopaminergic treatment.

#### Control cohorts

Though the complete DUPARC protocol solely concerns de novo PD subjects, there is ample opportunity to interpret the assessed endpoints relative to appropriate control cohorts. Primarily, age- and sex-matched control subjects are recruited separately to ensure identical assessment techniques for the neuropsychological, gastroenterological and ophthalmological assessments, representing the three main domains of the protocol. In addition, appropriate control subjects for the ophthalmological assessments, including HC and over 1000 glaucoma patients, are available under a different IRB-protocol in the UMCG. These all received the ophthalmological assessments, including retinal imaging, according to the UMCG standard operating procedures, using the same OCT machine, during overlapping periods, to ensure maximal compatibility with the DUPARC data. Complementary, the gut microbiome and genetic assessments will be compared to control subjects from LifeLines, a three generation, population-based cohort study concerning 167.000 participants from the same geographical area in the northern part of the Netherlands [39]. Of these participants, biomaterials such as fecal samples and blood samples have been collected in two large subcohorts (*n* = 9.000 and *n* = 1.100) [40, 41]. In addition, 38.000 LifeLines participants, of a total of 53.000 participants of whom genotype data is available, have received the same genome-wide genetic assessment using the Illumina GSA-MD chip. Genotype information will eventually become available for all 167.000 LifeLines participants. To ensure compatibility, the LifeLines standard operating procedures for the gut microbiome and genetic analyses are also used in DUPARC. Biomaterial from selected LifeLines participants can be reanalyzed to assess possible batch effects. Moreover, stool frequency and consistency has been assessed using the same stool diary in DUPARC and LifeLines, allowing for the identification of LifeLines subjects with idiopathic constipation. Lastly, a large proportion of endpoints, including the neuropsychological assessments, will be assessed using norm-rated tools that depict the performance of the patient as a percentile corrected for relevant demographics, such as age and level of education.

### Study procedures

At baseline, study procedures start at home with the collection of biomaterials for genetic screening and the completion of gastroenterological assessments and various other questionnaires. After the home assessments, participants visit the UMCG during 2 days for PET and MR-imaging, as well as a complete neuropsychological, ophthalmological and clinical assessment. An overview of the baseline assessments is depicted in Fig. 1.

**Fig. 1 Fig1:**
[figure not shown]
Baseline recruitment and assessments from Q4 2017 to Q3 2020 of treatment-naïve de novo PD subjects through the collaborative network of PD treating neurologists Parkinson Platform Northern Netherlands (PPNN). 1. Study procedures start at home with 1a. the collection of a saliva sample for genetic screening; 1b. Assessments of gastrointestinal function and stool sample collection; 1c. questionnaire assessments. 2. Participants visit the University Medical Center Groningen (UMCG) on 2 days for 2a. a complete cognitive assessment; 2b. imaging; 2c. ophthalmological assessments; 2d. clinical assessments. * In a subset of participants, intestinal wall permeability will also be assessed using blood samples and a urinary excretion test. ** Hyposmia is also assessed using the Sniffin’ sticks. Source clipart: clipart-library.com

Participants will receive follow-up assessments after 1 and 3 years, with the intention of an extended follow-up with three-year intervals. After 1 year, participants are visited at home for a repeated gastroenterological, clinical and questionnaire assessment. During the three-year follow-ups the complete baseline assessments are repeated with the exception of the genetic and gastrointestinal assessments. All assessed endpoints and the time of assessments are presented in Table 2.

**Table 2 Tab2:** Overview assessments DUPARC

Assessments	Endpoint	Baseline	Follow-up 1 year	Follow-up 3 years
**Cognition**				
Montreal cognitive assessment	Cognitive screening	X	X	X
Rey auditory verbal learning test	Learning and memory	X		X
Location learning test	Learning and memory	X		X
Wechsler Adult Intelligence Scale IV: Digit Span	Learning and memory	X		X
Wisconsin card sorting test	Executive functioning	X		X
Letterfluency	Executive functioning	X		X
Hayling sentence completion test	Executive functioning	X		X
Stroop color word test	Complex attention	X		X
Trail making test	Complex attention	X		X
Vienna Test System Reaction time test	Complex attention	X		X
Boston naming test	Language	X		X
Semantic Fluency	Language	X		X
Test of everyday attention: Map search	Perceptual-motor function	X		X
Judgment of line orientation	Perceptual-motor function	X		X
Facial expression of emotion: Stimuli and tests	Social cognition	X		X
Dutch adult reading test	Premorbid intelligence	X		X
**Vision**				
Farnsworth D15, Lanthony D15	Color vision	X		X
Optical Coherence Tomography	Structural retinal imaging	X		X
HFA2 SITA Fast	Peripheral vision	X		X
Pelli Robson Contrast Sensitivity	Contrast sensitivity	X		X
Non-contact tonometry	Intraocular pressure	X		X
Visual acuity	Visual acuity	X		X
**Gastrointestinal function**				
16S rRNA gene and metagenomic sequencing	Fecal microbiome composition	X	X	
Stool diary (7 days)	Stool frequency and consistency	X	X	
Dietary diary (3 days)	Nutrient intake	X	X	
Fecal calprotectin	Intestinal wall permeability - inflammation	X		
Fecal alpha1-antitrypsin	Intestinal wall permeability - protein leakage	X		
Serum zonulin^a^	Intestinal wall permeability - mucosal barrier integrity	X		
Urinary sugar excretion test^a^	Intestinal wall permeability	X		
Serum LPS^a^	Intestinal wall permeability - microbial translocation	X		
**Other non-motor symptom assessment**				
Sniffin’ Sticks	Hyposmia	X		X
Non Motor Symptom Questionnaire	Non-motor symptoms screening	X	X	X
REM Sleep Behavioral Disorder Questionnaire	REM sleep behavioral disorder	X	X	X
Hospital Anxiety and Depression Scale	Anxiety and depression	X	X	X
Dutch Multifactor Fatigue Scale	Fatigue	X	X	X
Apathy Evaluation Scale	Apathy	X	X	X
Questionnaire for Impulsive-Compulsive Disorder in Parkinson’s Disease Rating Scale	Impulsive-compulsive disorder	X	X	X
**Motor assessment**				
MDS-UPDRS III	Motor functioning	X	X	X
Hoehn & Yahr	Disease severity	X	X	X
MDS-UPDRS IV	Motor complications dopaminergic medication		X	X
**Burden of disease**				
MDS-UPDRS II	Motor aspects of experiences of daily living	X	X	X
Utrechtse coping lijst	Coping	X	X	X
Parkinson’s Disease Quality of Life Questionnaire 39	Quality of life	X	X	X
Dysexecutive Questionnaire	Dysexecutive syndrome	X	X	X
Zarit Caregiver Burden inventory	Caregiver burden	X	X	X
**General information**				
Disease History		X	X	X
Demographics		X		X
**Imaging**				
FDOPA PET	Brain dopaminergic imaging	X		X
FEOBV PET	Brain cholinergic imaging	X		X
MRI brain – Resting State		X		X
MRI brain – Diffusion Tensor Imaging		X		X
MRI brain – Arterial Spin Labeling		X		X
MRI brain – T1		X		X
MRI brain – T2		X		X
MRI brain - Susceptibility Weighted Imaging		X		X
**Genetics**				
GSA-MD	Genome-wide genotyping	X		
**Blood samples**^a^				
Plasma EDTA (8 × 2 ml aliquots)		X		X
Serum (4 × 2 ml aliquots)		X		X
Buffy coat (2x)		X		X

*EDTA* Ethylenediaminetetraacetic acid, *FDOPA PET* 18Fluor dopamine positron emission tomography, *FEOBV PET* 18Fluoroethoxybenzovesamicol positron emission tomography, *GSA-MD* Illumina Infinium Global Screening Assay (MD variant), *HFA2 SITA Fast* Humphrey Field Analyzer 2 SITA 24–2 – Fast visual field perimetry, *LPS* Lipopolysaccharide; *MDS-UPDRS* Movement Disorders Society Unified Parkinson’s Disease Rating Scale, *MoCA* Montreal Cognitive Assessment, *MRI* Magnetic Resonance Imaging

^a^Blood withdrawal and urinary sugar excretion tests are performed in a subset of participants

### Data management

Data are stored in an electronic Case Report Form (eCRF) using Castor, a Good Clinical Practice (GCP) certified electronic Data Capture (EDC). Data unfit for storage in the eCRF (eg. imaging and metagenomic data) are stored on local secured servers at the UMCG. The metadata are stored in the eCRF. Study monitoring will be performed by in-house study monitors of the UMCG. Depending on the type of data and associated privacy regulations, data from the DUPARC project will be made publicly available or will become available via the corresponding author, upon reasonable request.

### Sample size

Since most objectives of the DUPARC cohort study concern a first assessment in treatment-naïve de novo PD subjects, a formal power calculation is hampered, as no adequate estimation of the expected effect sizes can be provided. However, the effect sizes previously reported in already treated PD subjects with longer disease duration are mostly expected to be larger than the effect sizes in our cohort. Therefore, a power calculation based on previous reports will provide us with a minimum number of participants to include, to assess the most important endpoints within the domains of cognition, gastrointestinal function and vision.

The primary objective related to the cognitive domain is to establish the relationship between cognitive impairment and pre-synaptic cholinergic degeneration in de novo PD patients. This will be analyzed using cholinergic PET-imaging with FEOBV in combination with neuropsychological assessments covering all cognitive domains, including complex attention, learning and memory, executive function, perceptual-motor function, language, and social cognition. Because of the novelty of FEOBV, previous research using FEOBV-PET in PD is limited. Significant results were found in a small group comparing PD and control subjects [18]. Cross-sectional comparisons between PD subgroups have included between 15 and 79 PD patients, with significant results [42]. The size of the DUPARC cognition data is therefore expected to be sufficient for group and sub-group analyses, as well as detailed correlational research on the specific cognitive domains. Because of the great heterogeneity at baseline in both cognitive performance and cortical cholinergic innervation in PD, such a large cohort is needed for correlational analyses [43, 44].

The main objective within the gastrointestinal function domain is the comparison of the gut microbiome composition with HC. Though a power calculation for metagenomic analyses is not possible, we think our sample size will be sufficient to do these analyses, because previous studies already reported significant differences with far smaller sample sizes varying between 10 and 72 included PD subjects. Only two treatment-naïve subgroups of 12 and 39 PD subjects have been investigated in previous studies, reporting fewer taxonomic differences in the treatment-naïve group, compared to already treated subjects. The DUPARC gut microbiome data therefore surpasses most PD gut microbiome studies in sample size, and is by far the largest treatment-naïve dataset, allowing for more robust microbiome composition signatures and correction for confounders.

Regarding the domain of vision, the most recent meta-analysis on OCT imaging in PD has reported overall mean effect sizes of 0.45 for several retinal cell layers, comparing HC to PD subjects [33]. For a similar effect size, with an alpha of 0.05, and a two-tailed comparison of means, a sample size of 79 subjects for each group would be sufficient to achieve a power of 0.80.

The sample size of 150 participants therefore clearly surpasses the expected numbers needed to assess the primary objectives within the key domains of DUPARC. Nevertheless, a sample size of 150 participants is still necessary, as the anticipated effect sizes of various biomarkers in treatment-naïve de novo PD subjects is expected to be lower, compared to treated PD subjects with longer disease duration. In addition, to find biomarkers indicative of PD subtypes, the PD sample not only has to provide both case and control samples for a subtype comparison, but also the intergroup differences are expected to be lower if PD subgroups are compared. Our sample size of 150 participants will most likely allow for binary and trinary subtype comparisons, given the aforementioned samples sizes required to distinguish PD from HC. Lastly, the sample size also needs to be larger than calculated to account for participants who will be lost to follow-up. For this purpose, 180 participants will be included at baseline to account for 30 drop-outs and non-PD cases, in order to ensure a sample size of 150 participants.

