### Cognition

Cognitive dysfunction is a common non-motor symptom in PD that greatly influences the quality of life of patients. Mild cognitive impairment (PD-MCI) is already present in 25–30% of newly diagnosed patients and is considered an important risk factor for the development of PD dementia [7, 8]. The cognitive profile in PD is highly heterogeneous, with multiple cognitive domains affected.

The underlying pathology of cognitive impairment in PD is complex and includes the degeneration of multiple neurotransmitter systems, of which the cholinergic system is thought to be of particular importance [9–11]. In vivo cholinergic imaging studies revealed cholinergic deficits in PD patients compared to control subjects, with the cholinergic loss being even more pronounced in PD patients with dementia, suggesting a direct relationship between cholinergic denervation and cognitive decline in PD [12–14]. However, these findings are based on indirect Positron Emission Tomography (PET) imaging with a tracer binding to acetylcholinesterase. Although acetylcholinesterase is considered to be a reliable target for cholinergic imaging, it is located both on pre- and postsynaptic membranes, and also binds postsynaptically on non-cholinergic neurons [15, 16]. Recently, the selective PET tracer [^18^F]Fluoroethoxybenzovesamicol (FEOBV) was introduced and validated [17, 18]. This tracer binds presynaptically to the vesicular acetylcholine transporter and is a more sensitive and regional cholinergic marker compared to the cholinesterase binding tracers [17, 18].

Combining selective dopaminergic and cholinergic imaging with detailed neuropsychological assessment in a longitudinal cohort of de novo, treatment-naïve PD patients, provides the opportunity to explore the exact role of the cholinergic system in specific cognitive domains, to identify sensitive biomarkers of cognitive decline, and explore future therapeutic targets. We hypothesize that (1) in newly diagnosed, treatment-naïve PD patients, a significant proportion of patients will show cognitive impairment related to regional cortical and subcortical cholinergic denervation; (2) baseline regional cholinergic denervation will be a predictor of cognitive decline in PD over time.

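### The protocol's own 79-per-group figure does not support three-way subtype comparisons with 150 patients, and supports two-way comparisons only approximately

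*Protocol article*

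**What the plan says.** The Sample size section under Methods/design makes one formal calculation, for vision. It takes a meta-analysis of retinal imaging that "reported overall mean effect sizes of 0.45 for several retinal cell layers, comparing HC to PD subjects". "with an alpha of 0.05, and a two-tailed comparison of means", it concludes that "a sample size of 79 subjects for each group would be sufficient to achieve a power of 0.80".

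The section then explains why 150 patients are still wanted. For subtype biomarkers, both sides of the comparison must come from within the PD sample, and "also the intergroup differences are expected to be lower if PD subgroups are compared". The next sentence concludes: "Our sample size of 150 participants will most likely allow for binary and trinary subtype comparisons". The reason it gives is "given the aforementioned samples sizes required to distinguish PD from HC".

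The other sizes in the section are those of previous studies: 10 to 72 PD subjects and treatment-naïve subgroups of 12 and 39 for the microbiome, and 15 to 79 for comparisons between PD subgroups in the cognition paragraph. None comes with an effect size or a power figure. Enrolment at baseline is 180, to leave 150 after drop-outs and non-PD cases.

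**The concern.** The conclusion does not follow from its stated reason. If 79 per group are needed to tell PD from HC, and the 150 patients must themselves be divided, no equal division into two or three reaches 79. The sentence just before also expects a smaller effect between subtypes, which raises the requirement above 79.

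Subtypes are named in the overall aim, and subtype comparison is one of the reasons given for the sample of 150. A stated sufficiency invites readers to treat a null comparison between three subtypes as informative, when a pair of groups of 50 would miss a difference as large as the one between PD and HC about four times in ten.

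**Working it through.** **Inputs from the article.** d = 0.45; two-sided alpha 0.05; target power 0.80; 150 PD patients; 180 enrolled. **Assumptions, because the article gives no figure.** Equal subtype sizes as the best case; d of 0.40, 0.35 and 0.30 to illustrate smaller subtype effects; Bonferroni for three pairs as one possible multiplicity adjustment.

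**1. Reproduce the 79.** Normal approximation: n per group = 2(1.960 + 0.842)² / 0.45² = 2 × 7.85 / 0.2025 = 77.5, so 78. The two-sample t-test gives 78.49, so 79. The article's figure reproduces, and power at 79 per group is 0.80.

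**2. Divide the sample.** 150 / 2 = 75 and 150 / 3 = 50. Reaching 79 per group takes 2 × 79 = 158 PD patients for two subtypes and 3 × 79 = 237 for three. With Bonferroni for three pairs the t-test needs 105 per group, or 315 in total.

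**3. Power at those sizes.** The noncentrality is δ = d × √(n₁n₂ / (n₁ + n₂)). At d = 0.45 it is 0.45 × √37.5 = 2.76 for 75 v 75 and 0.45 × √25 = 2.25 for 50 v 50. Power of the two-sided t-test:

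| Groups compared | d = 0.45 | d = 0.40 | d = 0.35 | d = 0.30 |
|---|---|---|---|---|
| 75 v 75 (150, two equal) | 0.78 | 0.68 | 0.57 | 0.45 |
| 50 v 100 (150, two unequal) | 0.73 | 0.63 | 0.52 | 0.41 |
| 50 v 50 (150, one pair of three) | 0.61 | 0.51 | 0.41 | 0.32 |
| 50 v 50, Bonferroni (alpha 0.05/3) | 0.43 | 0.34 | 0.25 | 0.18 |
| 90 v 90 (all 180, two equal) | 0.85 | 0.76 | 0.65 | 0.52 |
| 60 v 60 (all 180, one pair of three) | 0.69 | 0.58 | 0.48 | 0.37 |

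**4. An overall three-group test instead of pairs.** With 3 × 50 patients and a largest difference of 0.45, one-way ANOVA has power 0.50 if the third mean lies midway (f = 0.45 × √(1/6) = 0.184), and 0.63 if it coincides with one of the other two (f = 0.45 × √2 / 3 = 0.212). Neither reaches 0.80.

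**5. Smallest d detectable with power 0.80 (t-test, 150 patients).** 75 v 75: 0.46. 50 v 100: 0.49. 50 v 50: 0.57, or 0.66 with Bonferroni.

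**The case against.** Several points on the other side have weight.

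- *The binary shortfall is small.* At d = 0.45 it is four patients per group and about two points of power. This stands. A clear binary failure needs a smaller effect, which the section expects but does not quantify.
- *The baseline sample may exceed 150.* The 30 extra enrolments cover both later drop-outs, who still have baseline data, and non-PD cases; the split is not given. With 158 or more PD patients an equal binary comparison at baseline reaches 79 per group. This stands for d = 0.45. It does not help the trinary comparison: even if all 180 counted, 60 v 60 gives 0.69.
- *The reason given refers to several sizes, not only to 79.* True, and groups of 50 or 75 lie within or above most of the precedents. But significant results in small studies do not show adequate power, and only the 79 was calculated.
- *The wording is hedged and the cohort is for discovery.* The hedge does not repair a reason that points the other way, and the section does not call these comparisons exploratory.

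A reader might also infer that the cognition paragraph's statement that its data are "therefore expected to be sufficient for group and sub-group analyses" falls with this one. The documents do not support that: it rests on the 15-to-79-patient precedents, and no cholinergic effect size is given against which to test it. Nor should the retinal d be carried to the microbiome-by-subtype objective (number 11 in Table 1), for which the section declines a power calculation, or to a split by mild cognitive impairment, which the subtype sentence does not name.

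**Conclusion.** The sentence is wrong as written, to different degrees in its two parts. The trinary claim is unsupported: power is 0.61 per pair at the full PD-versus-HC effect, 0.43 with Bonferroni, and below 0.80 even with all 180 enrolled. The binary claim holds approximately (0.78 at 75 v 75), and only if subtypes differ from each other as much as PD differs from HC, which the section itself does not expect. At an assumed d of 0.40 the binary power is 0.68, and at 0.30 it is 0.45.

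These figures assume equal subtypes, the most favourable case, and use the retinal effect because it is the only one the article quantifies. They test the article's reasoning and do not establish the power for other endpoints. A reader might conclude that the whole subtype aim is shown to be underpowered, or that the cohort is too small for its main comparisons. The documents support neither: true subtype effects are unknown, and 150 PD patients exceed the 79 needed for PD versus HC. The matter is of moderate weight.

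**What to change.** Replace the sentence on binary and trinary comparisons with the smallest effects detectable at 80% power with 150 patients: d about 0.46 for two equal subtypes, and about 0.57 for a pair among three equal subtypes (0.66 with Bonferroni for three pairs). Add that unequal splits need larger effects, for example 0.49 for 50 v 100. Label subtype comparisons, the trinary ones in particular, as exploratory. If baseline comparisons are to use more than 150 patients, state how many confirmed PD cases are expected.

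The change is to wording only. It needs no extra patients and leaves recruitment and the PD-versus-HC sizing as they are. Its cost is a less favourable stated sensitivity for subtypes. Removing the sub-group sentence from the cognition paragraph, or making continuous phenotype scores the main subtype analysis, is not required.
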